### Monitoring and reporting

2.8

Professional investigators will monitor the safety of included patients. Patients will be withdrawn from the trial if investigators believe they suffered risks based on medical reasons. Detected serious adverse events will be submitted to the related medical ethical committee for further evaluation within 1 month after the occurrence. All adverse events will be updated on the clinicaltrials.gov. Investigators can examine detail of the adverse events online.

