### Study design

2.2

This is a multi-center, prospective development study. The method of PPR using the bladder peritoneum flap in laparoscopic ELAPE is at the development stage. And this protocol fulfills the requirement of IDEAL framework stage 2A.^[6]^

Approval of the ethics committee has been obtained from the ethics committee of West China Hospital, Sichuan University (2019 No. 194). The present study was registered on the clinicaltrials.gov (NCT04177407) on November 27, 2019. For adopters from other institution, approval of the local ethic committee will be required. Procedure development with reasons for changes will be presented to the institutional review board for further assessment. Benefits and risks of the study will be informed to participants. Only participants who signed an informed consent form and agree to participate will be included in this study. Participants have the right to quit the study at any time without any reason. In emergency circumstances, surgeons have the right to end the study. Data of the details will be stored in a database and published after the trial.

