### Collection and analyses of data

2.6

Surgery related data collection. Surgical videos of all the included patients will be evaluated by the major center (Department of Gastrointestinal Surgery, West China Hospital of Sichuan University). Intraoperative information of primary tumor, operation time, data related to pelvic peritoneal reconstruction, postoperative recovery and postoperative pathology will be collected. Intraoperative complications are evaluated by operators during the surgery.

Follow-up data collection. Follow-ups will be performed by professional officers via outpatient service, phone or letter. The follow-up period is set as 1 year. Life quality is evaluated by EORTC QLQ-C30, EORTC QLQ-CR29 quality of life scale. Prostatic function is evaluated by international prostatic symptom score and bladder function is appraised by bladder residual urine. Schedule of follow-ups is listed in Table 2. Laboratory tests performed in none- research centers are accepted in the follow-up. However, radiological examination should be performed in the research centers.

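### Serious adverse events may take up to one month from occurrence to reach an unspecified ethics committee, and the only stated route to other operating surgeons is untimed online look-up

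*Protocol article*

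**What the plan says.** Section 2.8 (Monitoring and reporting) of the protocol article gives the rule for serious events: "Detected serious adverse events will be submitted to the related medical ethical committee for further evaluation within 1 month after the occurrence". It then describes how events are shared: "All adverse events will be updated on the clinicaltrials.gov", followed by "Investigators can examine detail of the adverse events online". Neither sharing sentence has a time limit.

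Section 2.2 (Study design) shows that more than one committee is involved: "For adopters from other institution, approval of the local ethic committee will be required". Section 2.6 says how events after discharge come to light: "Follow-ups will be performed by professional officers via outpatient service, phone or letter".

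The article also states powers to act locally. Section 2.8 has "Professional investigators will monitor the safety of included patients" and "Patients will be withdrawn from the trial if investigators believe they suffered risks based on medical reasons"; section 2.2 has "In emergency circumstances, surgeons have the right to end the study". Under section 2.6, operators assess intraoperative complications during the operation and the major centre evaluates the surgical videos of all included patients.

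**The concern.** The deadline, the recipient and the start of the clock are all written out. The point is therefore a rule that fits the study badly, not a detail left to a fuller document.

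This is an IDEAL stage 2a development study. The Discussion reports six earlier flap closures, three published and three more since. Section 2.5 adds two steps to the procedure, an anti-adhesion barrier and a fluorescence perfusion check, and the Discussion foresees further changes. Surgeons from other institutions are invited to adopt the technique (section 2.4), and section 3 says that all centres are recruiting. One stated aim is to modify the procedure to minimise the risk of complications. That aim depends on each surgeon learning promptly of serious events elsewhere.

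The rule has three weaknesses for this purpose:

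1. The limit is long for a technique performed in parallel at several sites while it is still being adjusted.
2. The word *related* does not identify the committee. With a local committee at each adopter site, similar events at two sites could go to two committees.
3. The clock starts when the event occurs, not when the site learns of it.

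At stake is how many further patients receive the flap before information from one site can inform the others.

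**Working it through.** **Sample size, needed only to set the pace of operations.** Section 2.7 gives 30 patients for a fall from 45% to 15%, α = 0.05, power 0.80, margin 0.05 and dropout 0.1. Sidedness is not stated. A one-sample test with two-sided α, null variance at 45% and effect 0.30 − 0.05 = 0.25 gives

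n = (1.96 × √(0.45 × 0.55) + 0.842 × √(0.15 × 0.85))² / 0.25² ≈ 26.03, rounded up to 27; 27 / 0.9 = 30.

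The figure of 30 is reproduced. It has no other bearing on this point.

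**Further flap operations in the permitted month.** The inputs are 30 patients (section 2.7) and a pre-study pace of 3 flap closures in 9 months (Discussion). The accrual period is not stated, so 12, 18 and 24 months are assumed. With monthly rate r and operations arriving as a Poisson process, the expected number in one month is r and the chance of at least one is 1 − exp(−r).

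| Pace | r per month | Chance of at least one |
|---|---|---|
| 3 in 9 months (pre-study) | 0.33 | 28% |
| 30 in 24 months (assumed) | 1.25 | 71% |
| 30 in 18 months (assumed) | 1.67 | 81% |
| 30 in 12 months (assumed) | 2.5 | 92% |

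The pre-study pace would need 30 / 0.33 = 90 months to reach 30 patients. That does not fit results expected in 2021 (section 3), so a multicentre pace should be faster. How much faster is not stated.

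**What the month bounds.** The one-month limit applies to submission to the committee. The online route to other investigators has no limit, so their delay may be shorter or longer than the one tabulated.

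**The clock.** Let d be the time in months from occurrence to detection. The time left to report is 1 − d. It shrinks as d grows and is negative once d exceeds 1. The restriction to detected events limits which events are reported, but it does not move the start of the clock. Small-bowel obstruction and perineal hernia count up to one year (section 2.3), and follow-up may be by phone or letter, so d > 1 is possible. Its frequency depends on the contact schedule in Table 2, whose content is not in the text available here.

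**The case against.** The strongest reply is that people can act at once. Investigators monitor safety and can withdraw patients, surgeons can end the study in an emergency, operators assess intraoperative complications as they happen, and the major centre reviews every video. One month is a ceiling. This is also a journal article, and a fuller protocol may hold site-to-sponsor forms and alerts.

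Much of this stands, and it rules out several stronger readings that a reader might infer:

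- *Nobody can act before the month is up.* The stated local powers contradict this.
- *The registry is the only route to other surgeons.* It is the only route stated, and another may exist in a document not shown.
- *A cluster of bladder injuries or failed flaps would be visible to nobody.* Section 2.3 classes bladder injury and flap devitalization as intraoperative, so the operator sees them and video review may show them to the major centre.
- *Late events come to light three to six months afterwards.* The 3-, 6- and 12-month times in section 2.3 belong to quality of life and to bladder and prostatic function. They are not given as the safety contacts.
- *Each local committee sees one or two cases, and the lead centre holds the stopping rule.* The article gives neither the number of centres nor the cases per centre. It assigns the stopping rule to nobody.

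The reply does not remove the core. The local powers require someone to know of the event already, and none of them informs another site. Video review has no stated timing and cannot show a later obstruction, hernia or wound failure. The limit, the recipient and the clock are explicit in the article, so a fuller document could add to them but would then have to replace this sentence.

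**Conclusion.** The point holds in limited form. The stated rule allows up to one month from occurrence, names no identifiable single recipient, and is paired with an untimed route to the other operating surgeons. Further flap operations *may* therefore precede any cross-site review. The documents do not show that they will.

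If the full month is used, the expected number is about 0.3 at the pre-study pace and 1.25 to 2.5 at an assumed accrual of 24 to 12 months. This rests on the assumed accrual period and on operations arriving at a steady rate.

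The fault in the clock does not depend on accrual: an event detected more than one month after it occurred cannot be reported in time. How often that happens cannot be judged without Table 2.

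The rule should be changed, because recruitment is under way and the change is cheap. It does not invalidate the study.

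**What to change.** Replace the reporting sentence in section 2.8 with a rule that does four things:

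1. Starts the clock at the site's awareness of the event.
2. Requires a prompt report from the site to the lead centre, for example within 24 hours.
3. Names the ethics committee or committees that receive all events from all sites.
4. Has the lead centre notify all operating surgeons of events possibly related to the procedure within a short fixed time, for example 7 days from the site's awareness.

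Keep the registry posting as a public record, not as the route to investigators. The 24-hour and 7-day figures are proposals and are not derived from the article.

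For an event known as soon as it occurs, 7 days in place of one month cuts the expected number of intervening flap operations by a factor of 7 / 30.4. That is from 0.33 to 0.08 at the pre-study pace, from 1.25 to 0.29 at 24-month accrual, and from 2.5 to 0.58 at 12-month accrual.

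The cost is protocol wording and e-mail notices by existing staff, with slightly more reporting work for the sites.

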### Patient and public involvement

2.9

Patients or public were excluded from the design of the trial and the selection of end points parameters. Patients are excluded from the recruitment and conduct of the trial either. Results of the present study will be published via medical journal(s). Participants of the study will be informed the outcomes by local monitors via phone or letter.

## Results

3

Patients recruitments is ongoing presently in all the centers involved in this study. Results are expected in 2021. Raw data are expected to be available to publication after the study via an open access database.

## Discussion

4

This multi-center, prospective development study is an IDEAL framework stage 2a study. Through this stage of study, we hope to:

(1)modify the bladder peritoneum flap closure to minimize potential risks of complications;(2)make the procedure refine enough at the end of stage 2a study to allow replication in later IDEAL stage study;(3)evaluate if this procedure could be adopted by other surgeons successfully;(4)evaluate the short-term clinical, technical and safety outcomes of the bladder peritoneum flap closure.

To prevent the small bowel or intraabdominal content from entering the pelvic dead space, several surgical methods have been adopted but there is no consensus on what the best method is. Generally, these methods can be divided into 2 categories: partition techniques and filling techniques. Partition techniques separate the abdominal and pelvic cavity with closed pelvic peritoneum^[5,10]^ or prosthesis.^[11]^ Filling techniques are to fill the pelvic dead space with a pedicled omentoplasty,^[12]^ myofascial flap or breast prosthesis.^[13]^ The omentoplasty seems to be the most popular technique, especially in laparoscopic ELAPE, in which suturing of pelvic peritoneum is sometimes technically demanding.^[5,10]^ However, a recent meta-analysis demonstrated that the omentoplasty is associated with increased risk for PH and perineal wound complications because non-vital omentoplasty may cause pelvic infection and subsequent complications.^[12,14]^ Traditionally, pelvic peritoneum is primarily closed after ELAPE by a running suture, barbed suture or Hem-o-lok clips.^[5,10]^ In some scenarios, reconstruction of pelvic peritoneum is difficult because of high tension. Modifications could be made to reduce the tension, such as making a shallow incision on both sides of the surface of pelvic peritoneum.^[5]^ Nevertheless, if there is no redundant pelvic peritoneum coverage, especially when the patient has a rigid pelvis after neoadjuvant radiation, either conventional or modified pelvic peritoneum closure is not feasible. Under these circumstances, even surgeons who routinely perform PPR may choose not to close the pelvic peritoneum. Currently, to our knowledge, there is no other studies on PPR regarding these situations. Our novel technique using the bladder peritoneum flap to reconstruct pelvic peritoneum in laparoscopic ELAPE could offer a new option to colorectal surgeons.

PPR is a well-accepted procedure to prevent perineal wound complications and intestinal obstruction in open abdominoperineal resection (APR).^[15]^ Despite this, there are only few evidences of application of PPR in laparoscopic APR/ELAPE. Yan et al recently reported that patients with PPR has a lower rate of perineal surgical site infection, delayed perineal healing, ileus and PH compared to patients without pelvic perineum reconstruction.^[5]^ To be noticed, in their study, the rate of PH was 0% in patients with pelvic perineum reconstruction, but it was based on data during the hospitalization. Similarly, Xu et al^[16]^ used Hem-o-lok clips to reconstruct pelvic peritoneum in laparoscopic APR for 22 patients with low rectal cancer or anorectal cancer, and there was no PH after 3 months. In the study of Wang et al,^[10]^ they compared the outcomes between patients with PPR along with primary perineal wound closure and patients with biological mesh closure for perineal wound without PPR. Their results showed that PPR was associated with shorter postoperative hospital stay and lower cost. The 1-year surgical outcomes were comparable between PPR with primary closure and biological mesh closure and there was no 1-year PH. In our previous study reporting 33 cases of laparoscopic ELAPE with PPR, there was also no symptomatic PH after 12 months follow-up and only 1 intestinal obstruction (3.0%, 1/33). Therefore, based on evidences from literatures and our own experience, we routinely perform PPR in laparoscopic ELAPE.

In the previous stage 1 study,^[2]^ we reported 3 cases using the bladder peritoneum flap to reconstruct pelvic peritoneum in patients with a rigid pelvis undergoing laparoscopic ELAPE In the past 9 months, we performed another 3 bladder peritoneum flap closure for patients with a rigid pelvis. Patient selection was extremely strict as we only perform this procedure in patients after neoadjuvant radiotherapy. As mentioned above, fibrosis in the pelvis is not the only condition for the failure of conventional PPR. In obesity patients or patients with bulky tumor, the pelvic perineum coverage may also be insufficient.^[5]^ Therefore, to accelerate the inclusion of patients, we would expand our inclusion criteria and not limit to patients with neoadjuvant radiation.

In this prospective development study, we would make some modifications, with the intention to minimize the potential risks of the bladder peritoneum flap closure. First, we would use an anti-adhesion barrier to protect the rough surface of the bladder and the flap. A study of Watanabe^[17]^ showed that the usage of anti-adhesion can reduce the incidence of postoperative adhesive SBO (0.0% vs 4.6%). Guidelines also suggest the usage of adhesion barriers as adjuvants in peritoneal reconstruction.^[18]^ We hope the application of anti-adhesion barrier could lower the risk for adhesive SBO. Second, we will use intraoperative ICG fluorescence after the bladder peritoneum flap closure to evaluate the vitality of the flap, if the vascular perfusion via ICG is poor or delayed, which indicates devitalization of the flap, the case will be counted as a failure and the pelvic peritoneum will not be closed thereafter. The incidence of flap devitalization would be objective parameter to reflect if the adopters have mastered the flap harvest step. Last, during the stage 2 study, further evolving of procedure may be utilized and will be reported in detail in the final article.

In conclusion, the bladder peritoneum flap closure may serve as an option to reconstruct pelvic peritoneum in patients who are not eligible for conventional pelvic peritoneum closure in laparoscopic ELAPE, but proof of which is much needed.
